### STATISTICAL ANALYSIS PLAN

#### Statistical methods

Standard statistical methods such as linear and logistic regression with SPSS software will be used to study the impact of vitamin D supplementation and/or maternal 25(OH)D concentrations, and relevant covariates, on main outcomes.

If needed, logarithmic transformation will be used to normalize skewed variables. Outcome measures will be analyzed according to the intention-to-treat principle.

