### Primary outcomes

Primary outcomes of the study are bone strength measured by peripheral quantitative computed tomography (pQCT) and incidence of parent-reported infections at age 2 years.

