### Statistical methods

Standard statistical methods such as linear, logistic and Tobit and moderation analytic strategies with R/SPSS/MPlus will be used to study the impact of vitamin D supplementation and/or 25(OH)D concentrations, and relevant covariates, on main outcomes.

If needed, logarithmic transformation for nonnormal variables is performed in order to achieve normal distribution. Main outcome measures are analysed according to intention-to-treat and protocol-based manner.

To account for multiple testing and control for the false detection rate (FDR), *p*-values from the analysis within primary/secondary analysis were used to derive an FDR-adjusted *p*-values with FDR-procedure setting the false discovery rate at 0.05.

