#### Primary outcomes

Primary outcomes of the study are childhood psychiatric symptoms at ages 6-8 years, assessed using the parent-reported Child Behavior Checklist (CBCL).

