#### Specific methods

#### Psychiatric symptoms

Psychiatric symptoms were assessed using the parent reported CBCL questionnaire. Results from the questionnaire are used to calculate scores for internalizing, and externalizing symptoms as well as total problems. Using ASEBA software, scores are converted to sex- and age-specific T-scores and dichotomized at 64 or above – scores above the cutoff point are considered to reflect clinically significant problems.

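### The CBCL amendment leaves its primary score, model, alpha and multiplicity rule unstated, so several primary treatment tests can go unadjusted

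*Combined protocol and SAP*

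**What the plan says.** The amendment for the current study has its own outcome statement: "Primary outcomes of the study are childhood psychiatric symptoms at ages 6-8 years", assessed with the parent-reported CBCL. No score is singled out. Its Psychiatric symptoms section adds: "Results from the questionnaire are used to calculate scores for internalizing, and externalizing symptoms as well as total problems". It then says that "scores are converted to sex- and age-specific T-scores and dichotomized at 64 or above".

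Its Statistical methods section reads: "Standard statistical methods such as linear and logistic regression with SPSS software will be used to study the impact of vitamin D supplementation". The same sentence extends the analysis to maternal 25(OH)D and covariates, and refers to the main outcomes collectively. After a rule on log transformation and a commitment to intention-to-treat, the section ends. It gives no alpha, lead score, lead model, testing order or multiplicity adjustment.

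The preceding neurodevelopment amendment does have such a rule. The last paragraph of its Statistical methods section opens "To account for multiple testing and control for the false detection rate (FDR" and adjusts p-values within the primary and secondary analyses at a false discovery rate of 0.05, citing the Benjamini-Hochberg paper. A significance level of 0.05 appears in the sample size sections of the main SAP and of the neurodevelopment amendment, but not in the CBCL amendment.

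**The concern.** Linear regression fits the T-scores and logistic regression fits the dichotomies, so naming both models for the main outcomes puts both forms of all three scores in play. Nothing ranks one above another. As written, any of up to six unadjusted p-values for the randomised comparison could be presented as an effect on a primary outcome.

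The timing adds weight. The amendment describes data collection in the past tense and the analysis in the future tense, so the choice of score and model may be made with the data already in hand. A rule fixed beforehand is what separates a primary result from a selected one.

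**Working it through.** The amendment states no error rate, alpha or sample size, so there is no figure of its own to reproduce. The check asks what error rate the text permits.

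**Inputs from the documents**
- Scores: 3 (Psychiatric symptoms section).
- Forms of each score: 2, the T-score and the dichotomy at 64 or above (same section).
- Models: linear and logistic regression (Statistical methods).
- Alpha: 0.05, taken from the sample size sections of the main SAP and the neurodevelopment amendment.

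**Assumptions, not in the documents**
- Two-sided tests.
- T-scores normal with mean 50 and SD 10. The cutoff is then z = (64 − 50)/10 = 1.4, with about 8.1% above it. Proportions of 5% and 10% were also tried.
- Correlation of internalizing with externalizing 0.3 to 0.8, and of each with the total 0.8 to 0.94.
- 170 or 400 children per arm.

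**Step 1: count.** 3 scores × 2 forms = 6 possible treatment tests. The maternal 25(OH)D tests are left out because the amendment's Background calls that aim secondary.

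**Step 2: independence reference.** P(at least one p < 0.05) = 1 − 0.95^k.
- k = 3: 1 − 0.95³ = 14.3%.
- k = 6: 1 − 0.95⁶ = 26.5%.

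The scores are correlated and each dichotomy comes from its own T-score, so these are upper references.

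**Step 3: correlated scores.** Simulation under no effect on any score, with a two-sample comparison of means for each T-score and a two-proportion test for each dichotomy as a stand-in for logistic regression. Results at 400 per arm, 20,000 replicates:

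| Correlations (int–ext / with total) | 3 continuous | 6 tests | 1 score, both models | 6 tests, Benjamini-Hochberg |
|---|---|---|---|---|
| 0.3 / 0.8 | 10.5% | 20.4% | 9.1% | 4.2% |
| 0.5 / 0.85 | 10.2% | 19.3% | 9.0% | 4.2% |
| 0.6 / 0.88 | 9.2% | 18.2% | 8.7% | 3.9% |
| 0.8 / 0.94 | 8.4% | 17.0% | 9.3% | 4.0% |

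At 170 per arm the six-test figures were 17.7% to 20.4%. Over the wider grid, with 5% to 10% above the cutoff, six tests gave about 16% to 21% and three continuous scores about 8% to 11%. A separate run with Wald logistic tests gave 15% to 16% at the strongest correlations, hence 15–21% overall. With only about 3% above the cutoff, six tests gave 11% to 17%.

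**Step 4: after adjustment.** With no effect on any score every rejection is false, so the false discovery rate equals the chance of any false finding. Benjamini-Hochberg at 0.05 gives about 4%, for the six tests or for the three continuous scores. The smallest p-value, standing alone, must reach 0.05/3 = 0.017 with three tests or 0.05/6 = 0.008 with six.

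**The case against.** A reader might infer that the plan commits to testing every score by both models at 0.05, that it withdraws the earlier false discovery rate rule, and that the risk is therefore 20%, four times nominal. The documents do not support any of these as stated.

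- **Six tests at 0.05.** The amendment introduces its models only as examples, assigns none to a named score and states no alpha. Six tests is the natural reading, but it is a reading.
- **Withdrawal of the adjustment.** The text is silent. As an amendment to an existing plan, it could be taken to leave the earlier rule in force. Against that, it rewrites the methods section, repeating the transformation rule and intention-to-treat but not the adjustment, and the earlier amendment is tied to a different report. Even if the rule carries over, it works within the primary analyses, and nothing says which CBCL tests those are.
- **The 20% figure.** It depends on the six-test reading and on correlations and a proportion above 64 that the documents do not give. With three continuous scores the inflation is about twofold.

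A reader might also set the amendment beside the main protocol's "Primary outcomes of the study are bone strength measured by peripheral quantitative computed tomography (pQCT) and incidence of parent-reported infections at age 2 years" and infer that the trial's primary outcomes were replaced. The amendment's Background already calls this a follow-up study building on earlier work, so relabelling would add little.

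It is also fair to object that nothing ranks T-scores above dichotomies, since the plan ties the cutoff to clinical importance, and that choosing a family now may be post hoc. Both points stand and shape the fix. They do not remove the gap.

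**Conclusion.** The concern holds as one of incomplete specification with a measurable consequence. The CBCL amendment declares psychiatric symptoms primary, provides three correlated scores in two forms, and states no lead score, lead model, alpha or multiplicity control, where the preceding amendment did state a control.

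Under no effect, at two-sided 0.05, the chance of at least one false primary finding is roughly 15–21% if all six tests are run and about 8–11% if only the three continuous scores are primary. The first range assumes roughly 5% to 10% of children above the cutoff and the correlations listed; it falls if fewer children exceed 64. Every multi-test reading examined exceeds 5%. What the documents do not settle is which reading applies, and that is itself the defect.

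**What to change.** In the Statistical methods section of the CBCL amendment, before the treatment comparison is analysed, define the primary family and its error control. One wording:

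*The primary family for the comparison of the randomised arms is the internalizing, externalizing and total-problems T-scores, each analysed by linear regression. P-values are two-sided and adjusted by the Benjamini-Hochberg procedure at 0.05. The dichotomies at 64 are secondary, analysed by logistic regression and adjusted in the same way within their own family.*

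Naming one score and one model as primary would serve equally well. If any data have already been analysed by arm, apply the procedure to all six tests instead. In either case, state when the rule was set.

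This needs SAP wording and one adjustment step, with no new data. The downside is a stricter threshold for an isolated result: about 0.017 with three tests, or about 0.008 with six, instead of 0.05. If all p-values in a family are at or below 0.05, the procedure still rejects them all. The procedure controls the false discovery rate, so the 4% figure applies where no score is affected; it is not a familywise guarantee once some effects are real.
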